		**Study period**						
		**Eligibility**	**Allocation**	**Post-Allocation**			**Close-out**	
	**Timepoint**	** *–t_**1**_* **	** *t_**0**_* **	** *t_**1**_* **	** *t_**2**_* **	** *t_**3**_* **	** *t_**4**_* **	** *t_***x***_* **
		**Day of ECMO**		**7 days after CaRe-ECMO**	**14 days after CaRe-ECMO**	**30 days after CaRe-ECMO**	**90 days after CaRe-ECMO**	**Discharge day^*^**
Enrollment	Eligibility check	X						
	Informed consent	X						
	Randomization		X					
Assignment	CaRe-ECMO group		X					
	Control group		X					
Variables	Demographics		X					
	Clinical characteristics		X					
	Rate of ready for ECMO weaning			X	X	X	X	
	Rate of ECMO weaning			X	X	X	X	
	Total length of ready for ECMO weaning							
	Total length of ECMO weaning							
	Rate of mechanical ventilation weaning			X	X	X	X	
	Total length of mechanical ventilation							
	All-Cause mortality			X	X	X	X	
	Rate of major post-ECMO complications			X	X	X	X	
	Diaphragmatic thickness and mobility							
	ECMO unit LOS							X
	Total hospital LOS							
	Total cost for hospitalization							
	CPC			X	X	X	X	X
	ADL			X	X	X	X	X
	HRQoL			X	X	X	X	X

*CaRe-ECMO, cardiopulmonary rehabilitation on extracorporeal membrane oxygenation; LOS, length of stay; CPC, cerebral performance category; ADL, activities of daily living; HRQoL, health-related quality of life*.

* *Discharge day refers to discharge from ECMO unit and it may variate according to recovery process of patients*.

Baseline demographics and clinical characteristics, directly from the medical files at randomization, will also be collected including but not limited to the following information: age, gender, main diagnosis, comorbidities (diabetes mellitus, hypertension, respiratory infection, or others), the Acute Physiology and Chronic Health Evaluation II (APACHE II) score, ECMO mode (VV-ECMO or VA-ECMO), length in hour since mechanical ventilation, partial pressure of arterial oxygen/fraction of inspired oxygen (PaO_2_/FiO_2_) in mm Hg, positive end-expiratory pressure (PEEP), tidal volume in ml/kg of predicted body weight, respiratory rate in breaths/min, plateau pressure in cm of water, driving pressure in cm of water, arterial blood pH, PaO_2_ in mm Hg, partial pressure of arterial carbon dioxide (PaCO_2_) in mm Hg, N-terminal pro-B-type natriuretic peptide (NT-proBNP) in pg/ml, creatine kinase-MB (CK-MB) in ng/l, cardiac troponin T (cTnT) in ng/l, and ejection fraction (EF) in percentage. The above data will be recorded in the Baseline Data Collection Sheet (Table 10). Apart from that, daily clinical monitoring for both the condition and ECMO running status of patient will be performed. The detailed information will be recorded in the Daily Monitoring Sheet (Table 11).

**Table 10 T10:** Baseline data collection sheet.

**Baseline data collection sheet**					
**Basic information**					
Name		Gender		Age	
Height (cm)		Weight (kg)		Bed number	
Inpatient ID		Phone number		BMI (kg/m^2^)	
Main diagnosis		APACHE II score		SOPA score	
Date of admission	___ / ___ / ___, ___: ___		Date of ECMO admission		___ / ___ / ___, ___: ___
Date of record	___ / ___ / ___, ___: ___				
**Medical history**					
Cardiovascular system	□ No □ Yes □ Cardiac surgery □ Cardiac intervention □ Myocardial infarction: □ Non ST-segment elevation □ ST-segment elevation □ Angina pectoris: □ Stable □ Unstable □ Structural heart disease □ Heart failure (□ New York Heart Association: □ I □ II □ III □ IV) □ Atrial fibrillation □ Hypertension				
Respiratory system	□ No □ Yes □ COPD □ Asthma □ Tuberculosis				
Cerebrovascular event and sequelae	□ No □ Yes □ Cerebral hemorrhage □ Cerebral infarction □ Dyskinesia □ Dysphagia □ Cognitive disorder □ Other______				
Diabetes	□ No □ Yes □ Type 1 diabetic mellitus □ Type 2 diabetic mellitus □ Impaired glucose tolerance				
Malignant tumor	□ No □ Yes □ Solid tumor □ Metastatic tumor □ Leukemia □ Lymphoma □ Other______				
Organ transplantation	□ No □ Yes				
Immune system disease	□ No □ Yes				
Medication history	□ Antiplatelet drugs: □ Aspirin □ Clopidogrel □ Dipyridamole □ Other______ □ Anticoagulants: □ Warfarin □ Dabigatran □ Rivaroxaban □ Heparin □ Other______ □ Antihyperlipidemic drugs: □ Statin □ Fibrates □ PCSK9 □ Other______ □ Antihypertensive drug: □β-receptor blocker □ ACEI □ ARB □ CCB □ Other______ □ Hypoglycemic drugs: □ Insulin □ Sulphonylurea □ Metformin □ Other______ □ Other______				
Personal history	□ Smoking history: Smoking index______ (Smoking index is a number of cigarettes smoked per day ^*^ years of tobacco smoking) □ History of alcoholism: Drinking index______g/day □ Dust and toxic exposure history				
Allergic history	□ No □ Yes □ Food □ Drug______				
Family history	□ No □ Yes □ Cardiovascular disease □ Cerebral disease □ Immune disease □ Endocrine disease □ Malignant tumor □ Other______				
**ECMO-Related information**					
Venue of ECMO operation	□ Out-of-hospital □ In-hospital				
ECMO cannulation	Drainage cannula □ Left □ Right Site: □ Femoral vein □ Axilla vein □ Internal jugular vein □ Right atrium Perfusion cannula □ Left □ Right Site: □ Femoral vein or femoral artery□ Axilla vein □ Internal jugular vein Whether additional drainage cannula is needed □ No □ Yes				
**Running status of ECMO**					
Indication	□ Cardiac □ Pulmonary □ ECPR				
ECMO type	□ VA-ECMO □ VV-ECMO □ Other______				
ECMO cannulation sites	VV-ECMO: □ No □ Yes (If yes, then fill the following items) □ Right femoral vein □ Left femoral vein □ Right internal jugular vein □ Left internal jugular vein □ Other______ VA-ECMO: □ No □ Yes (If yes, then fill the following items) □ Right femoral vein □ Left femoral vein □ Right internal jugular vein □ Left internal jugular vein □ Right femoral artery □ Left femoral artery □ Other______				
Distal collateral circulation	□ No □ Yes				
ECMO flow	ECMO blood flow______L/min ECMO gas flow______L/min ECMO FiO_2_______%				
Length from ECMO response to operation	______mins				
Length of ECMO operation	______mins				
Length of MV before ECMO	______days ______hours ______mins				
**First examination after ECMO**					
Blood routine examination	WBC______10^9^/L NE______% Hb______g/L PLT______10^9^/L				
Arterial blood gases	FiO_2_______% pH______ PO_2_______mmHg PCO_2_______mmHg BE______mmol/L ${\text{HCO}}_{3}^{-}$______mmol/L Lactate______mmol/l				
Inflammatory factors	C-reactive protein______mg/L Procalcitonin______ug/L Tumor necrosis factor______pg/mL IL-6______pg/mL Serum amyloid A______mg/L				
Biochemical examination	ALT______U/L AST______U/L TBIL______μmol/L DBIL______μmol/L ALP______U/L ALB______g/L BUN______mmol/L Cr______μmol/L Na^+^______mmol/L K^+^______mmol/L Cl^−^______mmol/L Ca^2+^______mmol/L				
Anticoagulation monitoring	Loading dose of heparin______IU/kg Maintenance dose of heparin______IU/kg APTT______s PT______s D-Dimer______ng/mL				
Antibiotic prophylaxis	□ No □ Yes______				
Cardiac function and myocardial injury markers	NT-proBNP______pg/ml cTnT______ng/L MyO______ng/L CK-MB______ng/L				
Electrocardiogram	□ Sinus arrhythmia □ Atrial arrhythmia □ Ventricular arrhythmia □ Supraventricular arrhythmia □ Junctional rhythm □ Other______ Ventricular rate______bpm				
Radiology	□ No □ Yes □ Pulmonary infection □ Pneumothorax □ Pulmonary edema □ Pulmonary atelectasis □ Pleural effusion/Hemothorax □ Cardiomegaly □ Pericardial effusion/Hemopericardium □ Cerebral edema □ Cerebral hemorrhage □ Ascites/Hemoperitoneum □ Ileus □ Other______				
Echocardiogram	EF______% VTI______ LVID______mm RVID______mm Valve □ Normal □ Abnormal □ Aortic valve (□ Moderate to severe aortic stenosis □ Moderate to severe aortic insufficiency) □ Mitral valve (□ Moderate to severe mitral stenosis □ Moderate to severe mitral insufficiency) □ Tricuspid valve (□ Moderate to severe tricuspid stenosis □ Moderate to severe tricuspid insufficiency) Structural heart disease □ No □ Yes □ Atrial septal defect □ Ventricular septal defect □ Tetralogy of fallot □ Endocardial cushion defect □ Single ventricle □ Other______ Pulmonary arterial hypertension □ No □ Yes Ventricular aneurysm □ No □ Yes				
Coronary angiography	□ No □ Yes Date of examination___ / ___ / ___ (If yes, then fill the following items) Stenosis □ No □ Yes Stenosis degree: I ≤ 25% II 26%-50% III 51%-74% IV ≥ 75% Left main artery: □ I □ II □ III □ IV Left anterior descending artery: □ I □ II □ III □ IV Left circumflex artery: □ I □ II □ III □ IV Right coronary artery: □ I □ II □ III □ IV Other______: □ I □ II □ III □ IV				
**Cardiac arrest (If ECPR, then fill the following items)**					
Venue of cardiac arrest	□ Out-of-hospital □ In-hospital				
Primary disease	□ Pulmonary □ Cardiac □ Anesthesia □ Other______				
Initial heart rhythm (Before CPR)	□ Ventricular fibrillation □ Pulseless ventricular tachycardia □ Pulseless electrical activity □ Cardiac standstill □ Other______				
Cardioversion or defibrillation	□ No □ Yes □ Unclear (If yes, then fill the following items) Drugs for cardioversion: □ Lidocaine □ Amiodarone □ Other______				
Length from cardiac arrest to CPR	Time of cardiac arrest___ / ___ / ___, ___: ___ Time of CPR___ / ___ / ___, ___: ___ Length______mins				
Length from CPR to ECPR	Time of CPR___ / ___ / ___, ___: ___ Time of ECPR___ / ___ / ___, ___: ___ Length______mins				

*ID, identified number; BMI, body mass index; ECMO, extracorporeal membrane oxygenation; APACHE, Acute Physiology and Chronic Health Evaluation; SOFA, Sequential Organ Failure Assessment; ECPR, external cardiopulmonary resuscitation; VV-ECMO, venovenous ECMO; VA-ECMO, venoarterial ECMO; FiO_2_, fraction of inspired oxygen; BE, base excess; MV, mechanical ventilation; CPR, cardiopulmonary resuscitation; ACEI, angiotensin-converting enzyme inhibitor; ARB, angiotensin receptor blocker; CCB, calcium channel blocker; PCSK9, proprotein convertase subtilisin/kexin type 9; COPD, chronic obstructive pulmonary disease; WBC, white blood cell; NE, neutrophil; Hb, hemoglobin; PLT, platelet; pO_2_, partial pressure of oxygen; pCO_2_, partial pressure of carbon dioxide; IL-6, interleukin-6; ALT, alanine aminotransferase; AST, aspartate aminotransferase; TBIL, total bilirubin; DBIL, direct bilirubin; ALP, alkaline phosphatase; AlB, albumin; BUN, blood urea nitrogen; Cr, creatinine; APTT, activated partial thromboplastin time; PT, prothrombin time; ACT, activated clotting time; NT-proBNP, N-terminal pro-B-type natriuretic peptide; cTnT, cardiac troponin T; MyO, myoglobin; CK-MB, creatine kinase-MB; EF, ejection fraction; VTI, velocity-time integral; LVID, left ventricular internal dimension; RVID, right ventricular internal dimension*.

**Table 11 T11:** Daily monitoring sheet.

**Daily monitoring sheet**							
**Name: ___ Gender: ___ Age: ___ Inpatient ID: ___ Bed number: ___** **Date of record: ___ / ___ / ___, ___: ___ Main diagnosis:**							
**Evaluation**	**Index**	**CaRe-ECMO Day 1**	**CaRe-ECMO Day 2**	**CaRe-ECMO Day 3**	**CaRe-ECMO Day 4**	**…**	**CaRe-ECMO Day X**
Consciousness	RASS score						
	GCS score						
	BIS index						
	NSE						
	S100-β protein						
	EEG						
Temperature	Bladder temperature (°C)						
	Axillary temperature (°C)						
Fluid intake and output	Intake (ml)						
	Output (ml)						
	Output excess (ml)						
Nutrition	Enteral nutrition (Y/N)						
	Parenteral nutrition (Y/N)						
	Total calories (Kcal)						
Blood routine examination	WBC (10^9^/L)						
	NE (%)						
	Hb (g/L)						
	PLT (10^9^/L)						
Inflammatory factors	C-reactive protein (mg/L)						
	Procalcitonin (ug/L)						
	Tumor necrosis factor (pg/mL)						
	IL-6 (pg/mL)						
	Serum amyloid A (mg/L)						
Biochemical examination	ALT (U/L)						
	AST (U/L)						
	TBIL (μmol/L)						
	DBIL (μmol/L)						
	ALP (U/L)						
	ALB (g/L)						
	BUN (mmol/L)						
	Cr (μmol/L)						
	Na^+^ (mmol/L)						
	K^+^ (mmol/L)						
	Cl^−^ (mmol/L)						
	Ca^2+^ (mmol/L)						
Arterial blood gases	FiO_2_ (%)						
	pH						
	PO_2_ (mmHg)						
	PCO_2_ (mmHg)						
	BE (mmol/l)						
	${\text{HCO}}_{3}^{-}$ (mmol/l)						
	Lactate (mmol/l)						
Anticoagulation monitoring	Maintenance dose of heparin (IU/kg)						
	APTT (s)						
	PT (s)						
	D-Dimer (ng/ml)						
	ACT (s)						
Cardiac function and myocardial injury markers	NT-proBNP (pg/ml)						
	cTnT (ng/L)						
	MyO (ng/L)						
	CK-MB (ng/L)						
Electrocardiogram	Heart rhythm						
	Ventricular rate (bpm)						
Echocardiogram	EF (%)						
	VTI						
	LVID (mm)						
	RVID (mm)						
Hemodynamics	Vasoactive agent (Y/N)						
	Type of vasoactive agent						
	Dose of vasoactive agent						
	Vasoactive inotropic score						
	Systolic blood pressure (mmHg)						
	Mean arterial pressure (mmHg)						
	Central venous pressure (mmHg)						
	Inferior vena cava (mm)						
	Inferior vena cava variability (%)						
Ventilator parameters	Mechanical ventilation (Y/N)						
	Mode						
	Tidal volume (ml)						
	Respiratory rate (bpm)						
	FiO_2_ (%)						
	PEEP/CPAP (mmHg)						
	PIP (mmHg)						
	P_plat_ (mmHg)						
	Minute ventilation (L/min)						
	Pulmonary compliance (ml/cmH_2_O)						
	Inspiratory resistance						
	Expiratory resistance						
Radiology	Pulmonary infection						
	Pneumothorax						
	Pulmonary edema						
	Pulmonary atelectasis						
	Pleural effusion						
	Cardiomegaly						
	Pericardial effusion						
	Cerebral edema						
	Cerebral hemorrhage						
	Ascites						
	Ileus						
Pathogenic microorganism	Bacteria (Y/N)						
	Fungus (Y/N)						
	Virus (Y/N)						
	Location of the microorganism						
	Name of the microorganism						
Running status of ECMO	ECMO mode						
	ECMO blood flow						
	ECMO gas flow						
	ECMO FiO_2_ (%)						
Adjuvant therapy	CRRT (Y/N)						
	IABP (Y/N)						
	Other (Y/N)						

*ID, identified number; ECMO, extracorporeal membrane oxygenation; RASS, Richmond Agitation Sedation Scale; GCS, Glasgow Coma Scale; BIS, bispectral index; NSE, neuron-specific enolase; EEG, electroencephalography; WBC, white blood cell; NE, neutrophils; Hb, hemoglobin; PLT, platelet; IL-6, interleukin-6; ALT, alanine aminotransferase; AST, aspartate aminotransferase; TBIL, total bilirubin; DBIL, direct bilirubin; ALP, alkaline phosphatase; ALB, albumin; BUN, blood urea nitrogen; BE, base excess; Cr, creatinine; FiO_2_, fraction of inspired oxygen; pO_v2_, partial pressure of oxygen; pCO_2_, partial pressure of carbon dioxide; PIP, peak inflation pressure; Pplat, plateau pressure; APTT, activated partial thromboplastin time; PT, prothrombin time; ACT, activated clotting time; NT-proBNP, N-terminal pro-B-type natriuretic peptide; cTnT, cardiac troponin T; MyO, myoglobin; CK-MB, creatine kinase-MB; EF, ejection fraction; VTI, velocity-time integral; LVID, left ventricular internal dimension; RVID, right ventricular internal dimension; PEEP, positive end-expiratory pressure; CPAP, continuous positive airway pressure; CRRT, continuous renal replacement therapy; IABP, intra-aortic balloon pump*.

### Blinding

Trial assistants from the allocation center responsible for randomization will be blinded to patients in both the groups. Each cardiopulmonary rehabilitation session provided by the therapists will be sheltered with a curtain. In the control group, an optimization procedure will be imitated as closely as possible, while no cardiopulmonary rehabilitation will be provided. This action may be helpful to blind the clinicians and nurses and mitigate any bias. Assessors, data analysts, and statisticians will be blinded to group allocation.

### Data Management and Monitoring

All the data will be entered into standardized electronic case report forms (eCRFs) and stored in a bespoke trial cloud database upon its collection. Data entry will be independently performed and dated by two trial assistants. Typos and missing data will be detected by this dual-track data entry mode. When discrepancies occur, consensus will be achieved by raw-data review or discussion. Confidentiality of data is assured by restricted access to the cloud database granted to authorized investigators only, for example, members of the Data and Safety Monitoring Committee (DSMC). The primary investigators, trial coordinators, the DSMC members, data analysts, statisticians, and trial assistants will meet periodically to: (1) monitor and review safety of patient; (2) request and perform interim data analyses; (3) review patient recruitment, accrual, and withdrawal; (4) discuss about continuing or modifying the trial; and (5) stop the trial upon any severe adverse events considered to have been caused by the CaRe-ECMO program (37).

### Sample Size Calculation

We considered the rate of ready for ECMO weaning being conservatively 50% higher in the CaRe-ECMO group than in the control group at CaRe-ECMO day 7 as a clinically meaningful effect, implying a hazard ratio (HR) of 0.5. Accordingly, we performed sample size calculation for the Cox proportional hazards model with an alpha error of 5% and a power of 80%, effect size of HR = 0.5, and overall event (ready for weaning) probability of 30% at CaRe-ECMO day 7 (increases from 30 to 45%) according to our retrospective data analysis and literature review (38). The needed sample size was estimated as *n* = 348, i.e., 174 per group. Due to the relative short observational period and the real-world situation (e.g., patients treated with ECMO therapy generally will not discharge till stable or death), accounting for 5% attrition according to their failing for fulfill of daily eligibility screening for cardiopulmonary rehabilitation during the therapeutic period, the target sample size is set at 366 (183 per group).

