### Statistical Methods

The demographic and clinical characteristics collected at randomization will be presented as means with SDs or medians with interquartile ranges for continuous variables and as percentages for categorical variables, as appropriate.

For all the outcomes, we will estimate differences in effect size between the groups on both the intention-to-treat (ITT) and per protocol (PP) basis (39). Categorical variables will be compared with the chi-square or Fisher's exact tests and continuous variables will be compared with the Student's *t*-test or the Wilcoxon signed-rank test, as appropriate. The time effect of day the time-to-event outcomes identified (e.g., rate of ready for ECMO weaning, rate of ECMO weaning, rate of mechanical ventilation weaning, all-cause mortality, and rate of major post-ECMO complications) between the groups will be estimated with the Cox proportional hazards regression analysis and graphically illustrated using the Kaplan–Meier methods until CaRe-ECMO days 7, 14, 30, and 90, respectively (40). Variables, including total length of ready for ECMO weaning, total length of ECMO weaning, total length of mechanical ventilation, ECMO unit LOS, and total hospital LOS, will be treated with time-to-event data and will be analyzed with mixed-effects ordered logistic regression (41). Secondary outcomes with normal and non-normal distributions, including CPC, ADL, HRQoL, and diaphragmatic thickness and mobility, will be estimated for group differences with mixed-effects linear regression (41).

Considering that part of patients will definitely not reach the primary endpoint, i.e., ready for ECMO weaning at CaRe-ECMO day 7 for sensitivity purpose, we will assess the heterogeneity of the treatment effect on primary outcome and secondary outcomes in pre-specified subgroups of interest as per baseline data to be collected at randomization (e.g., age, gender, main diagnosis, comorbidities, the APACHE II score, ECMO mode, length since mechanical ventilation) by using exploratory *post-hoc* sensitivity adjusted analyses for any corresponding statistical methods mentioned above.

Interim analysis will be scheduled halfway through enrollment to check that there are no serious issues with respect to sample handling or data collection.

All the analyses will be conducted at a two-sided alpha level of 5% and will be performed using the Stata version 16 (StataCorp, College Station, Texas, USA) or other software, as appropriate.

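### The sample-size derivation is wrong as written: 30% to 45% readiness implies HR 1.68, not 0.5, and the stated Cox inputs give about 218 patients, not 348

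*Protocol article*

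**What the plan says.** All the relevant figures stand in the Sample Size Calculation section of the protocol article. The target effect is a readiness rate "being conservatively 50% higher in the CaRe-ECMO group than in the control group at CaRe-ECMO day 7", which the section takes "as a clinically meaningful effect, implying a hazard ratio (HR) of 0.5". It then describes a sample-size calculation for a Cox model "with an alpha error of 5% and a power of 80" per cent, with "effect size of HR = 0.5" and an "overall event (ready for weaning) probability of 30% at CaRe-ECMO day 7 (increases from 30 to 45" per cent). The result is 348 patients, "i.e., 174 per group", raised to 366 for 5% attrition. The section does not say which arm is the reference for the hazard ratio.

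Statistical Methods settles the sidedness: "All the analyses will be conducted at a two-sided alpha level of 5" per cent. It assigns Cox regression to time to readiness, in line with Data Collection, which treats readiness as a time-to-event outcome. It also carries a general sentence: "Categorical variables will be compared with the chi-square or" Fisher's exact tests. Allocation is 1:1 (Enrollment, Randomization, and Allocation).

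**The concern.** Three things in one paragraph do not fit together.

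- **Effect size.** Becoming ready for weaning is a favourable event, so a benefit of CaRe-ECMO over control is a hazard ratio above 1. Even if the comparison is inverted, 0.5 does not correspond to 30% versus 45%.
- **Event probability.** The 30% is called the overall value and is also the starting point of the rise to 45%. With equal arms it cannot be both.
- **Sample size.** A hazard ratio of 0.5 is a large effect, and 348 looks too many for it at 80% power.

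The sample-size statement fixes the effect that the trial is designed to detect and the power it can claim. As printed, a reader cannot tell whether the target is the hazard ratio or the two proportions, and cannot reproduce the number. A ratio below 1 for a favourable event with no stated reference arm also invites a sign error when the result is reported.

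**Working it through.** **Inputs.** Two-sided alpha 5% (Statistical Methods); power 80%, HR 0.5, event probability 30%, rates 30% and 45%, N = 348 (Sample Size Calculation); 1:1 allocation. Normal quantiles: 1.960 and 0.842.

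**1. The plan's own figure from its own inputs.** Schoenfeld's formula for 1:1 allocation:

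events = 4 × (1.960 + 0.842)² / (ln HR)²

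For HR 0.5: 4 × 7.85 / 0.480 = 65.3, so 66 events. Patients: 65.3 / 0.30 = 218. Freedman's formula gives 71 events, and 71 / 0.30 = 237. Neither is near 348.

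The power of 348 on the stated inputs is Φ(√(348 × 0.30 / 4) × 0.693 − 1.960) = Φ(1.58), about 94%.

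The attrition step is not at issue: 348 / 0.95 = 366.3 and 348 × 1.05 = 365.4.

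**2. The hazard ratio implied by 30% and 45%.** Under proportional hazards, the proportion not yet ready in the treated arm is the control proportion raised to the power HR:

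HR = ln(1 − 0.45) / ln(1 − 0.30) = ln(0.55) / ln(0.70) = 1.68; inverse 0.60.

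In reverse, with 30% in the control arm:

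| HR, CaRe-ECMO vs control | Day-7 readiness, CaRe-ECMO |
|---|---|
| 0.5 | 1 − 0.70^0.5 = 16% |
| 1.68 | 45% |
| 2.0 (0.5 inverted) | 1 − 0.70² = 51% |

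Neither choice of reference arm makes 0.5 agree with 45%.

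**3. The overall event probability.** (30% + 45%) / 2 = 37.5%.

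**4. The Cox calculation with consistent inputs (HR 1.68, 37.5%).** Events: 117.7, so 118. Patients: 117.7 / 0.375 = 314, or 316 if events are rounded up first and the arms kept equal. Freedman gives 123 events and 328 patients. Power at 348: Φ(√(348 × 0.375 / 4) × ln 1.68 − 1.960) = Φ(0.99), about 84%.

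**5. Where 348 might come from.**

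| Route | Result |
|---|---|
| Two-sided Fisher's exact test, 30% vs 45%, power enumerated | 79.9% at 173 per group, 80.2% at 174 per group |
| Two proportions, normal approximation | 163 per group (326) without and 176 per group (352) with continuity correction |
| Cox, HR 0.5, 37.5% events, two-sided | 65.3 / 0.375 = 174 in total |
| Cox, HR 0.5, 30% events, one-sided | 52 / 0.30, about 174 in total |

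The first route gives 174 per group directly. The last two give 348 only if a total of 174 was taken as a per-group number, and the last also conflicts with the stated two-sided level. The document does not allow a choice between them.

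**The case against.** The best defence is that the number of patients is adequate whatever the text says. This stands. For 30% versus 45%, 348 patients give about 84% power by Cox and 80.2% by Fisher's exact test. Several stronger conclusions that a reader might draw are therefore not supported.

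- **That the 80% claim has no valid basis at all.** The derivation as described fails, but 174 per group does give 80% power for the document's own rates in an exact comparison of proportions.
- **That the number was computed with Fisher's test.** It fits, but the sample-size section never mentions that test, and a Cox total misread as a per-group figure would produce the same number.
- **That the trial is underpowered.** Lower figures can be produced: 54% to 64% if 50% higher is read as HR 1.5, 75% if HR 1.68 is paired with 30% overall events, and 70% if 30% is the overall rate and the arms are 24% and 36%. Each conflicts with the stated rise. HR 1.5 would bring 30% only to 1 − 0.70^1.5 = 41%, and 30% and 45% cannot average 30%.
- **That HR 0.5 means the plan assumes harm.** This holds only if the ratio is CaRe-ECMO versus control, which is not stated. Direction does not alter the sample size, because the formula depends on (ln HR)². The fair criticism is an unstated reference arm together with a wrong size.
- **That the primary test is unsettled because of the sizing.** Data Collection, Sample Size Calculation and Statistical Methods all treat readiness as time-to-event with a Cox model. The chi-square and Fisher sentence is general.

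The defence does not reach the hazard ratio, the double use of 30%, or the mismatch between the stated Cox inputs and 348. These are errors within one paragraph, and neither a separate analysis plan nor condensation for a journal explains them.

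**Conclusion.** The point holds as a misdescribed calculation. HR 0.5 should be 1.68 for CaRe-ECMO versus control (0.60 inverted). The overall event probability should be 37.5% if 30% is the control rate. The stated inputs lead to about 218 patients (237 by Freedman), and 348 would carry about 94% power on them, not 80%. The origin of 348 remains unknown, and no power shortfall is shown for the difference of 30% versus 45%.

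The figures assume proportional hazards up to day 7. They take 30% and 45% as the proportions ready by day 7 and count those as the events, without allowing for follow-up cut short by death or withdrawal. The rates themselves come from the investigators' retrospective data and literature review, and were taken as given.

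**What to change.** In Sample Size Calculation, remove the hazard ratio of 0.5 and the description of 30% as the overall probability. State instead: readiness by day 7 of 30% in the control group and 45% in the CaRe-ECMO group; hazard ratio 1.68, CaRe-ECMO versus control, with values above 1 favouring CaRe-ECMO; overall event probability 37.5%.

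Keep the Cox model and restate its power at 348 patients as about 84% (two-sided 5%), noting that about 118 events and 314 to 316 patients would suffice for 80%. The Fisher figure for the day-7 proportions (80.2% at 174 per group) may be added as a supporting calculation. The primary analysis should not be switched to that test on a guess about where 174 came from.

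The cost is a wording change here and in any matching text in the registry entry or analysis plan. The target stays at 366 and no patients are added.
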